### 2.8. Data Analysis

The analysis will be performed by using the statistical software R. Numeric variables will be expressed as mean (M) and standard deviation (SD), including the range, minima, and maxima. Beyond simple data and study variable descriptions, inferential analysis will be performed in order to determine possible significant relationships between the variables of the study.

A paired-sample Student’s t-test will be used to compare the means of the different sleep parameters of interest. T-test effect sizes are 0.2 (small effect), 0.5 (moderate effect), and 0.8 (large effect), so if the means of two groups do not differ by a 0.2 standard deviation, the difference is trivial, even if there is a statistically significant relationship. [62]. Bland–Altman plots will be used to assess the concordance between both devices for each of the sleep parameters (total sleep time, sleep efficiency, and wake after sleep onset). A positive bias indicates that the device tends to underestimate a variable when compared with PSG. A negative bias indicates that a sleep variable is overestimated [63]. Point estimations will be calculated, as well as their 95% confidence interval.

An epoch-by-epoch (EBE) (min × min) analysis will be performed in order to calculate the sensitivity (the proportion of epoch segments identified as a sleep state by the PSG that are correctly identified by Xiaomi), specificity (the proportion of epoch segments identified as a waking state by the PSG that are correctly identified by the Xiaomi wristband), and the level of agreement between both devices for light sleep identification (the proportion of PSG-classified N1 + N2 stages identified as light sleep by the Xiaomi wristband), deep sleep identification (the proportion of PSG N3 + N4 stages identified as deep sleep by the Xiaomi wristband), and REM sleep identification (proportion of PSG-classified REM stages identified as REM sleep by the Xiaomi wristband) [64]. Data analysis will include the cleaning or preprocessing, description, and processing of the stored data. The final aim of this workflow will be to obtain useful information that can be used for decision-making. During preprocessing, the wrong values of the dataset will be removed or corrected to avoid bias in the results. Subsequently, obtaining a descriptive statistic study that summarizes relations and distributions in a simple way will help us to know which processing strategy needs to be taken. When processing, information extraction will be performed.

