Recent studies have compared the measurements of these wristbands with those of actigraphy and PSG techniques. PSG involves different types of electrodes (electroencephalogram (EEG), electrooculogram (EOG), electromyogram (EMG), and electrocardiogram (ECG)) to classify the stages of sleep [42]. A few studies have shown that the usability of an ECG signal can determine the stages of sleep [43,44,45,46]. Nevertheless, some have considered the need for further research due to the insufficient quality of this classification compared to the combination of the other electrodes [47,48].

In general, wearable devices can determine the stages of sleep through a heart rate (HR) sensor, which measures the HR, and an accelerometer that detects movement. Previously validated wearable devices have shown a high precision and sensitivity, but also a low specificity and poor agreement in sleep-stage classification when compared with PSG [20,32,33,49,50]. It would be logical to expect these devices to measure sleep more accurately; however, according to these studies, there is a wide range of improvements that can still be accomplished [51,52]. As a result, this protocol has been designed to validate the Xiaomi Mi Smart Band 5 due to its low cost and high acceptance among users, as it is the best-selling fitness tracker [53]. This device has the capability of tracking the activity and HR of users, and classifies the user’s state as being awake or in light sleep, deep sleep, or REM sleep [54].

Therefore, this research focuses on determining whether sleep stages recorded by the new Xiaomi Mi Band 5 can effectively replace PSG sleep-stage classification in sleep-study participants. To this end, the following features will be calculated for both devices: total sleep time, sleep efficiency, sleep latency, and wake after sleep onset. Sleep stages will also be recorded.

Thus, the primary purpose of the present study is to validate the quality of the data generated by Xiaomi wearables when compared with the PSG technique from a hospital sleep unit.

The secondary objectives are: (1) to determine the total sleep time, sleep efficiency, sleep latency, and wake after sleep onset from both the wearable device and PSG; and (2) to examine whether the classification of sleep stages provided by wearable devices is comparable with classifications based on PSG.

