### 2.5. Justification of Sample Size

Differences equal or greater than 15 min in deep-sleep time between the measures of both methods are considered clinically relevant. Accepting a 0.05 alpha risk and a 0.1 beta risk (90% power) in a bilateral contrast, 43 subjects are needed to detect a difference that is equal to or greater than 15 min. Conservatively, a standard deviation of 30 for mean differences is assumed, according to previous studies [21,50,57].

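### The sample size and paired t-test are built to detect a mean difference, whereas the aim is validation, and the protocol's own 15-minute limit for deep sleep is never used in the analysis

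*Protocol article*

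**What the plan says.** The Introduction of the protocol article states that "the primary purpose of the present study is to validate the quality of the data generated by Xiaomi wearables when compared with the PSG technique". It also asks whether the band's staging "can effectively replace PSG sleep-stage classification in sleep-study participants". Both are questions of agreement.

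Section 2.5 fixes the clinical limit: "Differences equal or greater than 15 min in deep-sleep time between the measures of both methods are considered clinically relevant". The sizing is for a two-sided difference test ("Accepting a 0.05 alpha risk and a 0.1 beta risk (90% power) in a bilateral contrast"), it assumes that "a standard deviation of 30 for mean differences is assumed", and it concludes that "43 subjects are needed to detect a difference that is equal to or greater than 15 min".

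Section 2.8 says that a paired "t-test will be used to compare the means of the different sleep parameters of interest". Its one rule of interpretation is that "if the means of two groups do not differ by a 0.2 standard deviation, the difference is trivial, even if there is a statistically significant" result is obtained. It plans Bland–Altman plots for total sleep time, sleep efficiency and wake after sleep onset, and point estimates with 95% confidence intervals. It also plans an epoch-by-epoch analysis giving sensitivity, specificity and agreement for light, deep and REM sleep. No acceptance limit is attached to any of these, and the 15 minutes of section 2.5 does not reappear.

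**The concern.** The null hypothesis of the paired t-test is that the mean difference is zero. Rejecting it shows that the two methods differ on average. Failing to reject it shows only that the data could not exclude zero, which can happen because bias is small or because the differences are very variable. Neither result says whether the bias is smaller than the 15 minutes the protocol regards as relevant.

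The test can therefore mislead in both directions. A bias below 15 minutes can be reported as a difference, and a bias of 15 minutes can go undetected. For this test taken alone, more variable differences make a non-significant result more likely.

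Deep sleep is the most exposed variable. It drives the sample size, yet it is left out of the Bland–Altman list, so the t-test is the only named method that compares its minutes between devices. What is at stake is whether the planned analysis can support any statement about the validity of the variable for which the study was sized.

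**Working it through.** **Inputs** (protocol article, section 2.5): relevant difference 15 min in deep sleep; SD of paired differences 30, taken as minutes; two-sided alpha 0.05; power 90%; n = 43. SDs of 45 and 60 min, and true biases of 3, 5 and 10 min, are assumptions that show the range.

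**1. The stated sample size reproduces.** For paired differences, n = (z₀.₉₇₅ + z₀.₉₀)² × (SD/δ)² = (1.960 + 1.282)² × (30/15)² = 42.03, rounded up to 43. The number is not an arithmetic error. It is the size for a difference test. The exact noncentral-t power at n = 43 is 89.3%.

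**2. Where the t-test becomes significant.** The standard error is 30/√43 = 4.575 min. The critical value of t on 42 degrees of freedom is 2.018. The smallest significant observed difference is 2.018 × 4.575 = 9.2 min, well below 15.

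**3. How often the t-test gives each answer at n = 43** (noncentral t, with noncentrality = bias/(SD/√43)):

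| True bias (min) | SD (min) | Noncentrality | Significant | Not significant |
|---|---|---|---|---|
| 10 | 30 (planned) | 2.19 | 57% | 43% |
| 15 | 30 (planned) | 3.28 | 89% | 11% |
| 15 | 45 (assumed) | 2.19 | 57% | 43% |
| 15 | 60 (assumed) | 1.64 | 36% | 64% |

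At SD 60 an observed mean bias of up to 2.018 × 60/√43 = 18.5 min would remain non-significant, which exceeds the protocol's own limit.

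**4. The 0.2 SD rule.** The protocol does not say which SD is meant. If it is the SD of the paired differences, the cut-off is 0.2 × 30 = 6 min, which does not match 15 min. It would also have no effect at n = 43, because significance already requires 2.018/√43 = 0.31 SD.

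**5. An equivalence criterion using the protocol's 15 min.** Two one-sided tests at 5% conclude that there is no relevant mean bias when the 90% interval, mean ± 1.682 × SD/√n, lies inside ±15 min. At SD 30 and n = 43 the half-width is about 1.682 × 4.575 = 7.7 min. Simulated pass rates at n = 43:

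| True bias (min) | SD (min) | Pass rate |
|---|---|---|
| 0 | 30 | 89% |
| 3 | 30 | 81% |
| 5 | 30 | 69% |
| 15 | 30 | 5% |
| 0 | 45 | 39% |
| 0 | 60 | 5% |

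A bias at the limit passes in only 5% of studies, and greater variability lowers the pass rate. For 90% power at SD 30, 45 pairs are needed at zero true bias and 79 at a true bias of 5 min.

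**6. What equivalence of means does not show.** With zero mean bias and SD 30, the 95% limits of agreement are ±1.96 × 30 = ±58.8 min. Such a band would pass the mean criterion in 89% of studies, although an individual night could be wrong by about an hour.

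**The case against.** A reader might infer that the protocol treats a non-significant t-test as validation, so that a noisier band would pass. The document does not support that. It nowhere states such a rule and defines no pass at all. The variability argument also applies to the t-test alone. The Bland–Altman plots for three parameters would show wide limits for a noisy band, and the epoch-by-epoch analysis, which includes deep sleep, would show misclassification.

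Three further points favour the protocol. The 0.2 SD rule is meant to prevent over-reading of significance. The planned 95% confidence intervals may let a reader set the deep-sleep bias against 15 minutes without help. At the protocol's own SD, which it calls conservative, a 15-minute bias is missed in only 11% of studies; the larger miss rates rest on SDs that the document does not give. The study also describes itself as a pilot, and the Abstract and Conclusions say the band is not expected to replace PSG.

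Much of this stands and limits the claim. It does not remove the mismatch. The protocol states a validation aim and a 90%-power calculation, and fixes both the test and the sizing hypothesis, so this is not a detail left to an analysis plan. Epoch-by-epoch agreement is a proportion and does not address bias in minutes. The Bland–Altman list omits deep sleep, and the 0.2 SD rule is not tied to 15 minutes.

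**Conclusion.** The point holds in a limited form. The aim is agreement, whereas the sample size and the t-test address a mean difference, and the 15-minute limit is not carried into section 2.8. A non-significant result could be misread as agreement, but the protocol does not say it will be read that way.

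At n = 43 and SD 30, the t-test flags a true 10-minute bias, below the limit, in 57% of studies and misses a true 15-minute bias in 11%. The 43% and 64% miss rates apply only if the SD were 45 or 60.

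The figure of 43 is correct for what it calculates and comes close to serving an equivalence criterion, but only if the true bias is near zero. The results assume roughly normal paired differences, 43 evaluable pairs, and that the 15 minutes in section 2.5 can serve as a margin.

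**What to change.** In section 2.8:
- Judge mean bias in deep-sleep time by whether the 90% confidence interval of the paired mean difference lies within ±15 minutes (two one-sided tests).
- Keep the t-test as description, and state that a non-significant result is not evidence of agreement.
- Add deep sleep to the Bland–Altman analysis with 95% limits of agreement, because equivalence of means does not show agreement in individuals.
- Say which SD the 0.2 rule refers to, and that it does not override the 15-minute criterion.

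In section 2.5, restate the power of 43 evaluable pairs for this criterion at SD 30: about 89% at zero true bias, 81% at 3 minutes and 69% at 5 minutes.

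The cost is rewording of two sections, with no new data. The stated power becomes less favourable, noticeably so if the true bias is not zero. Keeping 90% power would take 45 pairs at zero bias or 79 at 5 minutes, so the investigators should either accept the lower figure openly or enlarge the sample.

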### 2.6. Outcomes

The outcomes will be the sleep-stage identification of PSG and the Xiaomi Mi Smart Band 5, and measurements of total sleep time, sleep efficiency, sleep latency, and wake after sleep onset.

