## 4. Conclusions

This project contributes to the validation of the sleep data obtained through the Xiaomi MiBand 5, making a comparison with the PSG data. Therefore, it is intended to determine whether the sleep parameters (TIB, SOL, WASO, SE, light sleep, deep sleep and REM sleep) are correctly measured through the Xiaomi MiBand 5.

The widespread use of these devices by the current society is not expected to replace the PSG. However, the information obtained by the wristbands about sleep is user-friendly in a domestic context, as this sleep data doesn’t need to be processed as in the case of the PSG. Thus, the use of these devices can help the population to be able to objectively determine whether they have difficulties in their sleep or not, as well as to promote healthy lifestyle habits, and if necessary, seek the advice of a healthcare professional.

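### The Bland-Altman list stops at total sleep time, sleep efficiency and WASO, so deep-sleep time (the variable the study is sized on) and sleep latency get no limits of agreement

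*Protocol article*

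**What the plan says.** Section 2.8 (Data Analysis) gives three between-device analyses:

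- a paired t-test on the sleep parameters of interest, in a paragraph that ends by promising point estimates with 95% confidence intervals;
- Bland-Altman plots "for each of the sleep parameters (total sleep time, sleep efficiency, and wake after sleep onset");
- an epoch-by-epoch analysis giving sensitivity and specificity for sleep against wake and, for light, deep and REM sleep, the share of PSG epochs of that stage that the band labels the same way.

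Other sections set a wider scope:

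- Section 2.5 sizes the study on deep sleep: "Differences equal or greater than 15 min in deep-sleep time between the measures of both methods are considered clinically relevant".
- Section 2.6 names as outcomes the stage identification and "measurements of total sleep time, sleep efficiency, sleep latency, and wake after sleep onset". The first secondary objective in section 1 lists the same four measures.
- Section 2.7 and Table 1 define time in bed and light, deep and REM durations as study variables.
- Section 4 states that "it is intended to determine whether the sleep parameters (TIB, SOL, WASO, SE, light sleep, deep sleep and REM sleep) are correctly measured" by the band.

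**The concern.** The Bland-Altman list is worded as covering every sleep parameter but contains only three, and it does not match the article's own outcomes, Table 1, conclusions or sizing variable. This is a stated list that conflicts with other stated text, so it is not simply detail left to a fuller document.

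The study asks whether one measuring device agrees with another. A comparison of means says whether the band is off on average. It does not say how far a single night's reading may lie from PSG, and section 3 looks ahead to a professional reading an individual user's data. Limits of agreement answer that question. If the plan is followed as written, the study reports none for the variable on which its sample size and its only stated clinical difference rest, or it adds them after the data have been seen.

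**Working it through.** **1. Coverage, variable by variable**

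| Variable | Where it is named | Bland-Altman | Epoch-by-epoch | Paired t-test |
|---|---|---|---|---|
| Total sleep time | 1, 2.6 | yes | no | yes |
| Sleep efficiency | 1, 2.6, Table 1, 4 | yes | no | yes |
| WASO | 1, 2.6, Table 1, 4 | yes | no | yes |
| Sleep latency | 1, 2.6, Table 1, 4 | **no** | no | yes |
| Deep sleep | 2.5, Table 1, 4 | **no** | stage sensitivity | yes |
| Light sleep | Table 1, 4 | **no** | stage sensitivity | yes |
| REM sleep | Table 1, 4 | **no** | stage sensitivity | yes |
| Time in bed | Table 1, 4 | **no** | no | yes |

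The t-test column assumes that the sleep parameters of interest in section 2.8 include all those in Table 1. The epoch-by-epoch column shows stage-level measures only; the sleep/wake sensitivity and specificity are not tied to one row.

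Of the seven parameters in section 4, two (sleep efficiency and WASO) get Bland-Altman, three (light, deep, REM) get an epoch-level measure instead, and two (sleep latency, time in bed) get at most the t-test. Of the four measures in section 2.6, three get Bland-Altman.

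**2. The plan's own sample size**

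Inputs from section 2.5: difference 15 min; SD 30, unit not stated and taken as minutes ("Conservatively, a standard deviation of 30 for mean differences is assumed"); two-sided alpha 0.05; power 90%.

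n = (SD × (z₀.₉₇₅ + z₀.₉₀) / difference)² = (30 × (1.960 + 1.282) / 15)² = 42.03, rounded up to 43.

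This matches the plan: "Accepting a 0.05 alpha risk and a 0.1 beta risk (90% power) in a bilateral contrast, 43 subjects are needed". It also shows that the 30 is being used as the SD of the paired differences in deep-sleep time.

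**3. What Bland-Altman would show for deep sleep with the same inputs**

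- 95% limits of agreement: bias ± 1.96 × 30 = bias ± 58.8 min.
- Ratio to the relevant difference: 58.8 / 15 = 3.9.
- 95% CI half-width of the bias at n = 43 (t with 42 df = 2.018): 2.018 × 30 / √43 = 9.2 min.
- 95% CI half-width of each limit: 2.018 × 30 × √(1/43 + 1.96² / (2 × 42)) = 15.9 min.

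If the true bias were zero and the differences normal, the share of nights differing by 15 min or more would be 2 × (1 − Φ(15/30)) = 2 × (1 − 0.6915) = 62%. At an observed SD of 30 min, the t-test would not be significant for any observed bias below about 9.2 min.

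No SDs are given for sleep latency, light sleep, REM sleep or time in bed, so nothing can be computed for them.

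**4. Whether the epoch-by-epoch analysis fills the gap**

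For deep sleep it is the proportion of PSG deep epochs that the band also calls deep. Epochs that the band wrongly calls deep do not enter it, so a band that labelled every epoch deep would score 100% while grossly overstating deep-sleep minutes. It gives neither a bias nor limits in minutes.

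**The case against.** The strongest reply is that the omitted variables are not left without analysis, and much of it stands.

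- A reader might infer that everything outside the list is left with a comparison of means. Section 2.8 does not support that: light, deep and REM sleep have a planned epoch-by-epoch level of agreement. Only sleep latency and time in bed have no analysis of their own beyond the t-test.
- A reader might infer that only two of the seven parameters in section 4 get any agreement analysis. Two get Bland-Altman, but three more get the epoch-level measure.
- A reader might infer that no bias will be reported for deep sleep. The paired comparison, with the promised point estimates and 95% CIs, gives the mean difference. The limits of agreement are what is absent.
- A reader might go further and argue from section 1, which says earlier devices showed high sensitivity "but also a low specificity and poor agreement in sleep-stage classification when compared with PSG", that the WASO bias must grow with true WASO and that constant limits would be wrong. The article gives no sensitivity, specificity or sleep duration from which to size such a trend, and whether the bias changes sign depends on the values assumed. Section 2.8 states only a sign convention for the bias and does not commit to constant limits. A Bland-Altman plot is also the usual place to see a trend.

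It is also fair to say that section 2.1 calls this a pilot study, that the sample size reproduces, and that nothing about design or data collection depends on the point. This lowers what is at stake, but the mismatch remains: neither the t-test nor a per-stage sensitivity gives limits of agreement for minutes.

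**Conclusion.** The point holds as a gap in the scope of the Bland-Altman analysis. As written, section 2.8 yields no limits of agreement for deep-sleep time, the variable behind the 15 min difference and the 43 participants. It also yields none for sleep latency, a named outcome, or for light-sleep minutes, REM minutes and time in bed, which section 4 says will be judged.

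For deep sleep the unreported limits would be about bias ± 59 min, roughly four times the 15 min difference. That figure assumes that the SD of 30 is in minutes, that it is the SD of the paired differences (the reproduced 43 supports this) and, for the 95% reading, that the differences are roughly normal. Section 2.5 uses the 15 min as a mean difference, so the ratio shows how much single-night spread a mean test can conceal. It is not a failed acceptance criterion. The sample size is not in dispute, and the documents support no figure for a WASO trend.

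**What to change.** In section 2.8, extend the Bland-Altman list to deep, light and REM minutes, sleep latency and time in bed, alongside total sleep time, sleep efficiency and WASO. For each, report the bias and both limits of agreement with 95% CIs. State that the deep-sleep bias and limits will be read against the 15 min difference of section 2.5. Keep the epoch-by-epoch analysis as a complement. At most, add that each plot will be inspected for a trend in the differences.

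The cost is a sentence or two in section 2.8 and five more plots from data that section 2.7 and Table 1 already plan to collect. The sample size stays at 43, which at the planning SD would give the deep-sleep bias to within about ± 9.2 min and each limit to within about ± 15.9 min.

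### A single mean bias read by its sign can misstate the band's wake-related error in good and poor sleepers, because that error is expected to change with the amount of wake

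*Protocol article*

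**What the plan says.** Section 2.8 compares the means of the sleep parameters by paired t-test and treats a difference below 0.2 SD as trivial, even when it is statistically significant. For agreement it states that "Bland–Altman plots will be used to assess the concordance between both devices for each of the sleep parameters", naming "total sleep time, sleep efficiency, and wake after sleep onset". It then fixes how the result is read: "A positive bias indicates that the device tends to underestimate a variable when compared with PSG", and "A negative bias indicates that a sleep variable is overestimated". Point estimates come with 95% confidence intervals. The section gives no step for a bias that varies with the level of the measurement.

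The same section plans an epoch-by-epoch analysis. Sensitivity is the share of PSG sleep epochs that the band also calls sleep. Specificity is the share of PSG wake epochs that the band also calls wake.

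On what to expect, the Introduction says: "Previously validated wearable devices have shown a high precision and sensitivity, but also a low specificity and poor agreement in sleep-stage classification".

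**The concern.** The t-test, the 0.2 SD rule and the signed bias each reduce the comparison to one average. That is a sound summary when the error is about the same for everyone. It is a poor one when the error depends on the quantity measured, and the plan's own definitions imply this for wake. A band that misses a fixed share of wake misses more minutes in a patient who is awake longer. A band that calls a fixed share of sleep wake adds more false wake minutes in a patient who sleeps more.

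Sections 2.2 and 2.3 recruit patients attending for any diagnostic test at a unit that sees insomnia, apnea, narcolepsy and other disorders, so a wide range of wake is plausible. The Discussion wants the band to help show who has a sleep disorder. Poor sleepers are therefore the group for whom a misstated error matters most.

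**Working it through.** **The plan's own figure.** Section 2.5 gives 43 subjects for a 15 min difference in deep sleep, SD 30, two-sided alpha 0.05 and 90% power. The paired normal formula gives (30 × 3.2415 / 15)² = 42.03, rounded up to 43. This reproduces, and nothing below changes it.

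**Inputs.** The definitions of sensitivity (se) and specificity (sp) come from 2.8. The documents give no values for se, sp, WASO or recording time, so those below are assumptions, shown as ranges. W is PSG wake and T the minutes after sleep onset. For WASO the formula is an approximation, because wake before onset is counted in latency.

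**Expected error.**
- Band wake = sp × W + (1 − se) × (T − W).
- PSG minus band: D(W) = (2 − se − sp) × W − (1 − se) × T.
- Slope on W: (1 − sp) + (1 − se), which is zero only for a perfect classifier.
- Sign change at W0 = (1 − se) × T / (2 − se − sp).

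**Point values**, with se 0.95 and T = 435, so (1 − se) × T = 21.75:

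| sp | slope | W = 20 | W = 60 | W = 120 |
|---|---|---|---|---|
| 0.40 | 0.65 | −8.75 | +17.25 | +56.25 |
| 0.50 | 0.55 | −10.75 | +11.25 | +44.25 |
| 0.60 | 0.45 | −12.75 | +5.25 | +32.25 |

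**Where the sign changes**, T = 435:
- se 0.98, sp 0.40: 8.7 / 0.62 = 14 min.
- se 0.92, sp 0.70: 34.8 / 0.38 = 92 min.

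On a wider grid (T = 480, se 0.90–0.98, sp 0.30–0.70) the slope is 0.32–0.80 and the sign change lies at 13–120 min.

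**The other two parameters.** In a fixed recording window, the total sleep time error is the total wake error with its sign reversed. Sleep efficiency scales with it. With 480 min in bed, se 0.95, sp 0.50 and W = 120, the wake error is 0.55 × 120 − 24 = +42 min. The band then overstates efficiency by 42 / 480 × 100 = 8.75 points.

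**What one mean and constant limits would show.** Simulated WASO was lognormal (mean 60, SD 45), with noise SD 15, se 0.95 and sp 0.40–0.60. If constant 95% limits were used, they would cover 98–99% of the third with least wake, 87–88% of the third with most and 58–63% of the highest tenth. Overall coverage stays near 95%, so the headline figure does not reveal the failure.

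**Does the mean look reassuring at n = 43?** It depends on both parameters:
- se 0.95: the t-test is significant in about 97%, 75% and 23% of samples at sp 0.40, 0.50 and 0.60.
- se 0.98, sp 0.40–0.60: it is significant in nearly all samples.
- se 0.92, sp 0.50: mean bias is about 0, since D(60) = 0.58 × 60 − 34.8 = 0. The t-test is non-significant in 94% of samples and the 0.2 SD rule calls the difference trivial in 79%. Yet the lowest and highest thirds are off by −21 and +27 min.

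**Can 43 patients show the trend?** Regressing the difference on the mean of the two methods gives p < 0.05 in 97–100% of samples at se 0.95 and sp 0.40–0.60, and in 91% at sp 0.70. A separate simulation let se and sp vary between patients. With narrow wake (mean 40, SD 20) and sp 0.70, it found the trend in only 50% of samples.

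**The case against.** The strongest reply is that the article states nothing false. Its sign rule is a correct convention for PSG minus device and speaks of a tendency; individuals depart from every mean. That stands.

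A reader might infer that the plan commits to constant limits of agreement. The text does not say so and never mentions limits, so the coverage figures show what would follow from constant limits, not what the plan promises.

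A trend would also be visible on a Bland–Altman plot, the epoch analysis will report specificity directly, and 2.8 leaves room for the descriptive results to guide later processing. This weakens the point without removing it. None of these steps is tied to how the bias is read, and the reading rule that is written down uses the mean alone.

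A reader might also infer that the mean bias will look small and the t-test will be non-significant, hiding the problem. The calculations do not support this in general: over much of the assumed range the t-test is significant. At se 0.98 and sp 0.40–0.60 the direction reverses only below about 14–21 min of wake, so there the issue is mainly size.

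Finally, the Introduction's statement that earlier devices had "high precision and sensitivity, but also a low specificity and poor agreement in sleep-stage classification" gives no figures and does not describe this band.

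**Conclusion.** The point holds in a limited form. Under the plan's own definitions, imperfect sensitivity or specificity makes the wake error change with the amount of wake. One mean bias can therefore misstate the size of the error at both ends of the range and, for some combinations, its direction. At the assumed central values the expected WASO error runs from −11 min at 20 min of wake to +44 min at 120 min. The direction changes at 14–92 min for sensitivity 92–98% and specificity 40–70%.

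This rests on assumed sensitivity, specificity, recording time and spread of wake. It also assumes that sensitivity and specificity do not themselves shift with wake in a way that cancels the slope. It does not show that the sign convention is wrong, that this band has low specificity, or that the mean will necessarily look reassuring. It is a worthwhile improvement to the agreement analysis, not a threat to the design or the sample size.

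**What to change.** In 2.8, for total sleep time, sleep efficiency and WASO:

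1. Regress the paired difference (PSG minus band) on the mean of the two methods, or on the PSG value, naming the choice in advance. Report the slope with its 95% CI.
2. Where the slope is not negligible, report bias and limits of agreement as a function of level (regression-based limits).
3. Keep the sign convention, but state over- or underestimation by level, not from one mean. Judge the slope by its size and interval and not by p < 0.05 alone, since a milder trend can be missed at this sample size.

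Log or ratio limits should not be required, because they are undefined when a recorded value is zero.

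The cost is a few lines of analysis text and R code on data already to be collected. Reporting becomes slightly more complex, and level-specific limits are less precise at n = 43, especially at the extremes.
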